## Abstract

**Introduction:**

This protocol is describing the first ever prospective, mock-efficacy, dose exploration trial design testing the feasibility of administering gabapentin in the acute setting as an intervention for neurorecovery. Gabapentin is an FDA-approved medication for treating seizures and postherpetic neuralgia and is used broadly off-label for neuropathic pain management for many conditions, including spinal cord injury. Emerging data suggests that when given early after spinal cord injury onset and in low-medium doses, gabapentin may have properties that promote recovery of neurological function. The objective of this trial is to assess the feasibility of conducting an efficacy trial in which gabapentin is started early after injury, is restricted in its dose, and is not used for pain management.

**Methods and analysis:**

Forty-two people aged 18 years or older with any level and any severity of spinal cord injury induced by a trauma will be enrolled, randomized, and have the first dose of study medication by 120 h post-injury onset. Participants will be randomly assigned to one of three groups: 600, 1,800 mg/day gabapentin, or placebo. Study medication will be given for a 90-day duration. Blinded assessments will be obtained at 7 days post-injury (baseline), 30 days post-injury (interim), after the 90-day treatment duration/approximately 3 months post-injury (end of treatment), and at 6 months post-injury (end of study). The key analysis parameters will evaluate feasibility of recruitment of target population, delivery of drug treatment protocol, maintenance of blinding, and retention of participants.

**Discussion:**

Outputs from this trial will inform research and clinical practice on the effects of manipulating gabapentin for non-pain management purposes in the acute setting and will guide the development of a properly powered efficacy trial of gabapentin as an intervention for neurorecovery in spinal cord injury.

**Ethics and dissemination:**

The study was approved by the MetroHealth Institutional Review Board (IRB21-00609) and registered at clinicaltrials.gov prior to enrolling any participants. Dissemination will include peer-reviewed publications, presentations at professional conferences and in the community, and through other healthcare and public venues.

**Clinical trial registration:**

www.ClinicalTrials.gov, identifier: NCT05302999; protocol version 1.1 approved 05/23/2022.

## Introduction

Gabapentin is an FDA-approved medication initially indicated for the treatment of seizures. Its action as an anticonvulsant is related to its ability to bind to the α2δ subunits of voltage-sensitive calcium channels (1). In addition, gabapentin has been approved for post-herpetic neuralgia, based on a multi-center randomized clinical trial reporting decreased average daily pain scores after an 8-week treatment period with the drug (2). It is thought that this analgesic mechanism is a result of astrocyte-derived thrombospondins promoting excitatory synapse formation via α2δ1 subunits (3). Although gabapentin has only two FDA-approved indications, it has been prescribed off-label for many years for multiple reasons, including management of neuropathic pain in spinal cord injury (SCI) (4, 5).

Gabapentin is recommended as a first-line treatment for SCI-induced neuropathic pain (6). Administration of 1,800 mg/day has shown good levels of pain relief in neuropathic pain and is a common target dose to minimize side effects (7). Maximal doses tested in clinical trials for SCI-induced neuropathic pain have ranged up to 3,600 mg/day and the major adverse events reported were dizziness and somnolence (8–10). Other side effects that are recommended to monitor include peripheral edema, weakness, fatigue, nausea, diarrhea, constipation, blurred vision, headache, and dry mouth (11). There is emerging evidence, both in animals and in humans, that gabapentin may also have a role in neurorecovery when administered early after SCI.

In rodent models of SCI, it has been shown that a single dose of gabapentin delivered 2–3 weeks post-injury resulted in a significant decrease in both spastic behavior and electromyography activity when compared to control animals (12) as well as a reduction in autonomic dysreflexia (AD) and tail spasticity in response to colorectal distension (13). Daily administration of low-dose (human equivalent dose of 648 mg/day) gabapentin for the first four weeks post-SCI in rats further suggests a role in mitigating evoked AD (14); high-dose (human equivalent dose of 5,184 mg/day) gabapentin did not have this effect (14). Additionally, it was recently demonstrated in a mouse model that daily administration of a low-medium dose (human equivalent dose of 1,296 mg/day) of gabapentin for 5 weeks post-SCI resulted in the blockade of excitatory synaptogenesis and sprouting of autonomic fibers innervating immune organs as well as nociceptive fibers that trigger AD (4). Functionally, this was correlated with a reduction in the frequency of spontaneous AD and severity of evoked AD as well as protection from SCI-induced immune suppression, which persisted for a month after stopping gabapentin (4). Daily administration of low-dose (human equivalent dose of 648 mg/day) gabapentin, started early after C5 hemisection in mice and continued for 4 months, has also been demonstrated to lead to sprouting of corticospinal tract fibers and improvement in forelimb function (15).

In humans, there is a growing body of evidence that gabapentin may have a positive effect on the amount of motor recovery as measured by the Total Motor Score (TMS) of the International Standards for Neurological Classification of SCI (ISNCSCI). This is based on retrospective analysis of the prospective European Multicenter SCI (EMSCI) observational study database. It was initially discovered, while performing an analysis related to pain, that individuals in the database who had been administered anticonvulsant medication within the 1st month post-injury gained an average of 7.3 additional TMS points at 1 year when compared to individuals who had not been administered anticonvulsant medication within the 1st month post-SCI (16). That cohort included individuals with tetraplegia and paraplegia as well as all levels of severity. A larger analysis confirmed the gain in motor recovery when anticonvulsants were started in the 1st month after injury (average of 6.3 additional TMS points at 1 year compared to those that were not administered anticonvulsants) and identified that the most frequently administered anticonvulsants were gabapentinoids (17). A gain of an average of 9 motor points is roughly equivalent to an improvement of one spinal segment, which can translate to a significant functional impact (as measured by the Spinal Cord Independence Measure) when the gain is in the cervical or lumbosacral regions (18). Good functional assessments of the thoracic segments are still lacking. An analysis of the Sygen database, a large (*N* = 797), well-designed clinical trial conducted primarily before gabapentinoids came to the market, revealed that non-gabapentinoid anticonvulsants given within 1-month post-SCI had no effect on total motor scores (19). Most recently, analysis of the EMSCI database enabled the longitudinal modeling of drug-by-time effect sizes on TMS point recovery with the largest effect size being when gabapentiniods were administered within the first 5 days following SCI (20). Interpretation of this effect size must be taken with caution, however, as it is based on a small number of cases (*n* = 14) and with no information regarding dose. To date, there have been no prospective studies evaluating early administration of gabapentin in humans with SCI.

### Objective

Overall, emerging preclinical and clinical evidence suggests that early initiation of low to medium doses of gabapentin and continued delivery for a range of 2 weeks to 4 months has a persistent, positive effect on motor and autonomic neurologic recovery. However, there are several questions that are important to understand before testing the efficacy of early administration of gabapentin as an intervention for neurorecovery. These revolve around the appropriate target population recruitment, the ability to deliver the treatment per protocol, the ability to maintain blinded assessors, and participant retention. The objective of the proposed study is to conduct the first ever prospective, dose-exploration trial to test the feasibility of early administration of gabapentin as an intervention for neurorecovery.

## Methods

### Trial design and setting

This is a prospective feasibility trial with randomized, controlled, and blinded features. To determine key issues regarding gabapentin dosing and restrictions, placebo use, and how those factors interplay with pain management, a mock efficacy design will be employed (Figure 1). The trial will feature a three-arm parallel group design, two arms receiving varying gabapentin doses, and the third arm receiving placebo. Placebo will be necessary for a future properly controlled efficacy trial. However, because gabapentin is used so ubiquitously for pain management, we need to understand the effect of withholding gabapentin for a 90-day period. Therefore, in the current study placebo is being administered primarily for feasibility reasons. This is a single-center study being conducted at an academic Level 1 trauma center in the USA that specializes in SCI acute care and rehabilitation.

**Figure 1 F1:**
[figure not shown]
Study Flow Chart. AIS, American Spinal Injury Association Impairment Scale; DPI, days post-injury.

### Participants and sample size

#### Eligibility criteria

Several of the inclusion criteria were intentionally kept broad because this is a study with key questions around enrollment and the protocol. Additionally, gabapentin has been used broadly and at much higher clinical doses in all levels and severities of SCI and there are no safety reasons to exclude specific injury levels or severities. Individuals will not be excluded based on race, ethnicity, or sex/gender. Individuals under the age of 18 will be excluded because this study will be the first prospective investigation of the safety and feasibility of administering gabapentin as a neurorestorative agent in adults with acute SCI.

Inclusion criteria:

Traumatic SCIAll levels of SCIAll severities of SCI, ASIA Impairment Scale (AIS) Grades A-DAge 18 years and olderAgree to participate and start study drug within 120 h post-injuryAdequate cognition and communication to provide informed consent.

Exclusion criteria:

Presence of moderate/severe traumatic brain injury as defined by Glasgow Coma Score less than 13 at 120 h post-injuryDocumented use of gabapentinoids at the time of injury.

#### Sample size

Studies analyzing feasibility are not intended to determine statistical significance, therefore traditional sample size calculations to power efficacy are inappropriate (21, 22). Rather, sample size should be large enough to yield useful data to answer the feasibility questions. There are several rules of thumb for determining a sample size for a feasibility study (typical range is 12–35 participants per arm; (23, 24). As described below, our most important neurologic outcome measure will be the ISNCSCI (all existing human data demonstrating effect of gabapentin on neurorecovery has been derived from the ISNCSCI). Differences in natural recovery due to injury severity could influence variability in ISNCSCI scores, with individuals that are AIS A or B being more similar than those that are AIS C or D (25). Therefore, we chose to stratify randomization into the 3 arms based on AIS grade (see Table 1). We will enroll 14 participants into each arm (with equal stratification of A–B and C–D in each arm). Therefore, our target sample size to complete the entire study will be 42.

**Table 1 T1:** Sample size and randomization cohorts.

**Arm**	**AIS A–B**	**AIS C–D**
Treatment 600 mg/day	7	7
Treatment 1,800 mg/day	7	7
Placebo	7	7

AIS, American spinal injury association impairment scale.

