### Randomization and intervention

#### Allocation and blinding

Participants will be randomized to 1 of 3 groups:

placebo,600 mg/day gabapentin, or1,800 mg/day gabapentin.

Group assignment will be stratified within each group based on AIS grade. A randomized stratified block design will be used with 3 blocks of size 7 within each cohort (AIS A–B and AIS C–D). A statistician will create a list under this design prior to enrollment of the first participant.

Blinded assessors will be designated for this study. The remainder of the study team will not be blinded to monitor all aspects of the trial. Blinding will be maintained by using the blinding plan described here to follow throughout the study.

The blinded assessors will be independent from the medical team and the research staff.Interactions between the blinded assessors and participants will be limited.Blinded assessments will be performed in a private room.The blinded assessors will be reminded prior to each assessment of the importance of blinding and to not engaging in extra “chit chat” with participants (and family/caregivers) or other study staff.Participants (and family/caregivers) will be informed of the importance of blinding overall at the beginning of the study and will be reminded prior to each blinded assessment to make sure he/she does not tell the blinded assessor(s) which group they are in.Blinded assessors will not review any previous blinded assessments.Blinded assessors will review the ‘Study Blinding Checklist' immediately before each blinded exam and will complete the ‘Blinding Verification Questionnaire' immediately after each blinded exam.If a participant becomes unblinded to his/her treatment group, every effort will be made to keep the blinded assessors blinded.If a participant develops neuropathic pain during the 90-day treatment window and the clinical team decides all other neuropathic pain treatments are ineffective, impractical, or contraindicated, study drug will be stopped and standard of care gabapentinoids may be used. The participant will not be withdrawn from the study, though, unless he/she desires to be withdrawn. Study drug will no longer be given, but any remain study visits will be completed. The blinded assessors will remain blinded of all knowledge that the study drug has been stopped.

Attempts will be made to blind participants, but as described below, the placebo and gabapentin capsules will not be identical.

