#### Primary feasibility assessments

The primary endpoint of this trial is feasibility. Table 3 lists the measures and quantitative benchmarks of success for the following four feasibility questions:

Can the target population be recruited?Can the drug treatment protocol be delivered?Can the assessors remain blinded?Will participants complete the study?

**Table 3 T3:** Analytical questions, measures, and benchmarks of success.

**Question**	**Measure**	**Quantitative benchmark of success**
Can the target population be recruited?	Number screened/month; number enrolled/month; reasons for not enrolling	Screen an average of 4/month; Enroll an average of 1/month
Can the drug treatment protocol be delivered?	Proportion of enrolled who receive the full drug treatment protocol (placebo arm; two gabapentin dose arms); number of dosing deviations/arm; reasons for dosing deviations	70% enrolled in placebo arm receive full dosing protocol; 70% enrolled in each gabapentin arm receive full dosing protocol
Can the assessors remain blinded?	Number of occurrences of unblinding; reasons for unblinding	5% or fewer occurrences of unblinding
Will participants complete the study?	Retention rate; reasons for dropout; proportion of planned assessments completed	70% of participants stay enrolled until the end of the study and complete 3 of the 4 assessment visits

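### The Sample size section gives 42 as the number completing the study, but the design enrols and randomises 42 and accepts 70% retention, which would leave about 29–30 completers

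*Protocol article*

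**What the plan says.** The abstract (Methods and analysis) states that "Forty-two people aged 18 years or older with any level and any severity of spinal cord injury induced by a trauma will be enrolled", and the same sentence has them randomised. The Sample size section says "We will enroll 14 participants into each arm", split equally between AIS A–B and AIS C–D, and draws from this: "Therefore, our target sample size to complete the entire study will be 42".

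Table 1 shows six cells of 7. Under Allocation and blinding, the randomisation list has three blocks of 7 in each of two AIS strata. In Table 3, the benchmark for the question of whether participants will complete the study is "70% of participants stay enrolled until the end of the study and complete 3 of the 4 assessment visits".

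The Sample size section also says that "traditional sample size calculations to power efficacy are inappropriate" for a feasibility study, and cites rules of thumb whose "typical range is 12–35 participants per arm". Under Secondary data analysis, the total motor score results and the upper limit of the 80% confidence interval for the SD are to inform the size of a later efficacy trial.

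**The concern.** The word that opens the target sentence presents it as a consequence of enrolling 14 per arm, but 3 × 14 is a count of people entering the trial. Calling it the number who complete assumes zero loss in an acute trauma population followed for six months. Elsewhere the same document plans to measure loss and would call up to 30% acceptable.

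At stake is what a reader takes the trial to deliver. Someone told to expect 42 completers would credit the end-of-study estimates, and the SD carried into the efficacy trial's sample size, with more precision than the design secures. The two meanings of 42 also imply different enrolment totals and different recruitment periods.

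**Working it through.** **Inputs, all from the protocol article**
- Enrolled per arm: 14, in 3 arms (Sample size)
- Cells: 3 arms × 2 AIS strata, 7 each (Table 1)
- List: 2 strata × 3 blocks × 7 (Allocation and blinding)
- Retention benchmark: 70% (Table 3)
- Recruitment benchmark: 1 per month (Table 3)
- Opening on March 14, 2022, and final enrolment estimated for 2026 (Recruitment)

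**Step 1. The plan's own figure.** 3 × 14 = 42; 6 × 7 = 42; 2 × 3 × 7 = 42. The figure reproduces exactly by three routes. Each route counts people enrolled or randomised, and none contains a dropout term.

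**Step 2. Completers = enrolled × retention.** Per-arm and per-cell values are averages and assume that losses are spread evenly.

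| Retention | Total of 42 | Per arm of 14 | Per cell of 7 |
|---|---|---|---|
| 100% | 42 | 14 | 7 |
| 90% | 37.8 | 12.6 | 6.3 |
| 80% | 33.6 | 11.2 | 5.6 |
| 70% | 29.4 | 9.8 | 4.9 |

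Only the first row matches the completion sentence. In whole people, 30 of 42 (71.4%) is the smallest count that meets the benchmark; 29 of 42 is 69.0%.

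**Step 3. The other reading.** If 42 completers were intended, enrolment = completers ÷ retention = 42 ÷ 0.70 = 60, or 20 per arm. That is 18 more than Table 1 and the list hold. At one enrolment per month from March 2022, 42 are reached about September 2025, which fits the estimated close in 2026. Sixty are reached about March 2027, which does not. The abstract, Table 1, the list and the timeline therefore all fit 42 enrolled, and the completion phrase is the one out of line.

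**Step 4. Effect on the planning SD (illustrative).** Assume normal data and an SD taken from completers only. The upper limit of the two-sided 80% interval is SD × √(df ÷ χ²₀.₁₀,df).
- Pooled over three arms: n = 42 (df 39) gives 1.18 × SD; n = 30 (df 27) gives 1.22 × SD. A sample size proportional to the variance rises by about 8%.
- Within one arm: n = 14 (df 13) gives 1.36 × SD; n = 10 (df 9) gives 1.47 × SD. The rise is about 17%.

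**The case against.** The best defence is that this is one loose phrase. The sum is right, every structural element agrees on 42 randomised, and the sentence may only mean the number needed to carry out the study. It stands that this is a fault of wording and not of arithmetic. The phrase is still not harmless: Table 3 uses the same idea of completing the study to mean retention, so the plain reading is a completer count.

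Several stronger conclusions are tempting, and the document does not support them.

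- **That about 30 are forecast to complete.** Table 3 sets 70% as the lowest retention that counts as success. The article predicts no dropout rate.
- **That the trial breaches a 12-per-arm minimum.** The 12–35 range is described as typical, is not adopted as a floor and is not tied to completers. The 14 enrolled per arm lie within it.
- **That the primary benchmarks are compromised.** Recruitment is a monthly rate, and the 5% unblinding criterion has no stated base. Only drug delivery and retention clearly use those enrolled, and dropout does not shrink that denominator.
- **That the motor score analysis rests on completers alone.** Secondary data analysis sets no such limit. Table 2 schedules ISNCSCI at four visits, so a late dropout can still contribute earlier scores, and stopping study drug does not end follow-up.
- **That a replacement rule is missing.** Such a rule may stand in the full protocol, which is not shown, so its absence here is no finding.

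**Conclusion.** The inconsistency is real. The article gives 42 both as the number entering and as the number finishing, and the two agree only with zero dropout. At the retention the plan would accept, 42 enrolled leaves about 29–30 completers, about 10 per arm and about 5 per arm-by-AIS cell.

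This rests on reading completion as Table 3 does, on no replacement of dropouts (none appears in the article), and on evenly spread losses for the per-arm and per-cell figures. The completer count is also only a guide to the number with an end-of-study score, because the benchmark lets a retained participant miss one of the four visits.

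Severity is minor to moderate. No primary benchmark or decision rule changes, and efficacy testing is disclaimed. The consequence falls on end-of-study descriptive estimates. It reaches the planning SD to the extent that end-of-study scores are used; there the effect is modest, about 8% on a variance-driven sample size if the SD is pooled and about 17% if it is taken within one arm.

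**What to change.** Replace the completion sentence in the Sample size section with wording such as:

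> 42 participants will be enrolled and randomised (14 per arm). If retention is at the 70% benchmark, about 29–30 (about 10 per arm) would complete the study.

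The conditional form matters: the text should not say that this number is expected. Add to Secondary data analysis that end-of-study total motor score SD estimates used to plan the efficacy trial may rest on that smaller number.

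The cost is a change of wording and a less favourable stated completer count. Table 1, the list, the timeline and the benchmarks stay as they are.

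If 42 completers is truly intended, the article should instead state 60 enrolled at the 70% benchmark and revise the abstract, Table 1, the randomisation list and the recruitment end date. That is a much larger change, and nothing else in the article points to it.

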#### Recruitment

Because time to enrollment is short and critical, acute traumatic SCI admissions will be prescreened daily. The study physician team will be informed of all acute traumatic spinal injuries as soon as possible so they can review the medical record and discuss potential eligibility. To aid in identification and approach, the study physician team is purposefully composed of a triad specialty including neurosurgery, trauma, and physiatry. All individuals who are considered potentially eligible will be approached to discuss the study. The study was opened for enrollment on March 14, 2022. It is estimated that the final participant will be enrolled in 2026.

